Because of the low incidence of bone/soft tissue sarcoma involving the pelvis, the PROSPER study was designed to be pragmatic, with generous eligibility criteria to avoid ineligibility (except for critical factors) and encourage collaboration among several CIRT centers. The CIRT centers participating in the PROSPER study use different RBE dose calculation models, dose fractionation schemes, and target volumes. We concluded that allowing these variations in the study was important to engage various international CIRT centers in one of the first multicontinental CIRT studies [29]. Although permitting such CIRT variability in our study will yield a heterogeneous cohort in the CIRT treatment arm that could obscure significant outcomes, we will scrutinize the results according to each treatment plan, which will be centralized, and evaluate the patterns associated with different functional outcomes, adverse events/treatment sequelae, and rates of local recurrence.

Inclusion criteria for enrollment in the PROSPER study are as follows: male and female patients aged at least 15 years, with an Eastern Cooperative Oncology Group Performance Status score of 2 or less, newly diagnosed disease, and histopathologic confirmation of pelvic chordoma, chondrosarcoma, osteosarcoma, Ewing sarcoma with bone involvement, rhabdomyosarcoma with bone involvement, or nonrhabdomyosarcoma soft tissue sarcoma with bone involvement. Patients will be required to provide written informed consent and complete questionnaires by themselves, or with assistance, and must agree to use adequate contraception if of childbearing age. Patients will be excluded if they have distant metastatic disease, as evidenced by clinical examination or imaging, or if they are receiving palliative-intent treatment, have recurrent disease, or have received prior radiotherapy to the tumor site or the surrounding area that would cause an overlap of radiotherapy doses in healthy tissues.

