CIRT facilities in Europe and Asia will enroll patients eligible for treatment with curative-intent CIRT in treatment arm 1. Mayo Clinic campuses in Arizona, Florida, and Minnesota will enroll patients in treatment arm 2 if they are examined in the Mayo Clinic orthopedic oncology or neurosurgery departments and deemed by a multidisciplinary team to be eligible to undergo definitive surgical treatment. Mayo Clinic (all campuses) will enroll patients in treatment arm 3 if they are examined in the Mayo Clinic radiation oncology department and deemed by a multidisciplinary team to be eligible to receive definitive treatment with PT.

### 2.1. Treatment Arm 1

Five CIRT centers participated in the development of the PROSPER study, including QST Hospital (Chiba, Japan), Shanghai Proton and Heavy Ion Center (Shanghai, China), Italian National Center for Oncological Hadrontherapy (Pavia, Italy), MedAustron (Wiener Neustadt, Austria), and the Heidelberg Ion Beam Therapy Center (Heidelberg, Germany). For all sites, CIRT is a standard-of-care treatment for unresectable sarcoma tumors involving the bone(s) of the pelvis. In accordance with the pragmatic approach of the PROSPER study, no strict guidelines were developed to specify target delineation, treatment planning, RBE dose calculation model, total dose, or dose fractionation. Each site has developed its own method for managing these tumors, which was a requirement for multicenter collaboration. However, Digital Imaging and Communications in Medicine (DICOM)-standardized treatment plans will be centralized for review, including variations in target selection and delineation, target coverage, organ at-risk (OAR) dose constraints, total dose, and dose fractionation. Adjuvant systemic chemotherapy is allowed according to institutional policies. 

### 2.2. Treatment Arm 2

Surgical treatment will be performed at all 3 Mayo Clinic campuses (Phoenix, AZ, USA; Jacksonville, FL, USA; Rochester, MN, USA). The specific type of surgical procedure will be at the discretion of the surgeon for each patient. Adjuvant radiotherapy and/or chemotherapy will be allowed according to institutional approaches to treatment. 

### 2.3. Treatment Arm 3

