### 2.4. Outcomes Measures

All patients will complete Patient-Reported Outcomes Measurement Information System-29 (PROMIS-29) and European Organisation for Research and Treatment of Cancer (EORTC) colorectal cancer–specific quality of life (QLQ-CR29) questionnaires at baseline and posttreatment time points.

Baseline patient-, disease-, and treatment-specific details will be collected and entered into our Research Electronic Data Capture (REDCap) system. After treatment is completed, the full radiation data set, including initial and any adaptive modifications to the data set (DICOM RT_PLAN, RT_STRUCT, RT_IMAGE, RT_DOSE), will be anonymized (except for the patient study number) and transferred to the Mayo Clinic DICOM database. Dose–volume histograms (DVHs) will be provided for the following OARs: the small bowel, large bowel, cauda equina, sacral plexus [30], femoral heads, rectum, and bladder. Oncologic outcomes and adverse events will also be entered in our REDCap system.

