The Kaplan–Meier method with likelihood ratio tests will be used to evaluate all clinical outcomes, which will include local recurrence, regional progression, distant metastases, progression-free survival, and overall survival, for each treatment arm. Subset and stratified analyses according to histopathologic characteristics will also be conducted for all time-to-event analyses. 

Exploratory analyses of local control between arm 2 and arms 1 and 3, treatment sequelae, and DVH data will be performed with standard logistic regression analysis of acute- (<6 months) and late-onset (≥6 months) treatment sequelae. Area under the receiver operating characteristic curve analyses will be performed for each DVH measure to determine the effect of the treatment modality on treatment sequelae, QOL, local control, and survival.

The participating CIRT centers will have considerable heterogeneity regarding patient selection, treatment prescription, total dose per fraction, target and OAR contouring, OAR constraints, and use of RBE dose calculation models. Therefore, CIRT data will be analyzed separately for each institution. In the unlikely event of marked differences in outcomes among these centers, sub-analyses will be performed, and we will consider publishing data for each (deidentified) institution separately.

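### ROC-AUC of DVH measures is given the task of determining the treatment-modality effect, but an AUC measures only how well dose discriminates and contains no arm contrast

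*Protocol article*

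**What the plan says.** All of this comes from the Protocol article.

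- **Method and purpose (section 2.6).** "Area under the receiver operating characteristic curve analyses will be performed for each DVH measure to determine the effect of the treatment modality" The outcomes follow directly: "on treatment sequelae, QOL, local control, and survival".
- **Companion analysis (section 2.6, preceding sentence).** Exploratory comparisons involving "DVH data will be performed with standard logistic regression analysis of acute- (<6 months) and late-onset (≥6 months) treatment sequelae". The article does not say whether this regression has a treatment-arm term.
- **Available dose data (section 2.4).** DVHs "will be provided for the following OARs: the small bowel, large bowel, cauda equina, sacral plexus", then femoral heads, rectum and bladder: seven organs at risk. The full DICOM radiation data sets are sent to a central database.
- **Dose scale (section 2).** The CIRT centres "use different RBE dose calculation models, dose fractionation schemes, and target volumes". Section 2.1 adds that "no strict guidelines were developed to specify target delineation, treatment planning, RBE dose calculation model, total dose, or dose fractionation".
- **Handling of CIRT heterogeneity (section 2.6).** "Therefore, CIRT data will be analyzed separately for each institution".
- **Surgical arm (Abstract and section 2.2).** Radiotherapy is optional.

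**The concern.** The sentence names a statistic and a purpose that do not match. This is not detail left for a later document: the method is named, its aim is named, and the method cannot meet the aim.

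An ROC curve for a DVH measure ranks patients by dose and asks how well that ranking separates those with the outcome from those without. It describes the relation of dose to outcome. A modality effect is a different quantity, a contrast in outcome between treatment arms.

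What is at stake is interpretation. A reader who takes the sentence at its word could report a high AUC as evidence that modality matters, or a low one as evidence that it does not. Neither follows. Section 2 presents scrutiny of the centralised plans as the response to permitted variation in CIRT technique, and the Discussion offers the results as benchmarks for later Phase III designs, so the output may be used beyond this trial.

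**Working it through.** The plan states no figure for the AUC analysis, so there is none to reproduce. The check is first logical, then illustrative.

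**1. What the AUC contains.** For a DVH measure X and a binary outcome Y,

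AUC = P(X of a patient with Y = 1 > X of a patient with Y = 0), with ties counted as one half.

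Only X and Y appear. Relabelling every patient's arm at random leaves X, Y and the AUC unchanged, while any estimate of a modality effect would change. The AUC therefore cannot carry that effect. This step needs no assumption.

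**2. Which patients can enter.**
- Arm 2 without radiotherapy: no DVH, so no contribution.
- CIRT by institution: each AUC holds one modality, so no contrast is possible even in principle.
- Proton arm alone: the same.
- CIRT and proton combined: two modalities are present, but step 1 still applies and the dose scales differ unless harmonised.

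**3. Illustration, common dose scale.** Assumed inputs: 200,000 patients per arm, dose with SD 1, and logit of risk = -1 + dose + modality effect.

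| Modality odds ratio | Risk difference | Pooled AUC | AUC within each arm |
|---|---|---|---|
| 1.0 | -0.002 | 0.740 | 0.741, 0.739 |
| 0.50 | -0.110 | 0.738 | 0.740, 0.744 |
| 0.25 | -0.192 | 0.732 | 0.742, 0.753 |

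The risk difference moves by about 0.19 and the pooled AUC by 0.740 - 0.732 = 0.008. Comparing the two within-arm AUCs does no better: they differ by 0.753 - 0.742 = 0.011 at an odds ratio of 0.25. Here the modality effect was added independently of dose, so the insensitivity is partly built in. The table illustrates step 1; it does not prove it.

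**4. Illustration, different dose scales.** Same model with no modality effect (odds ratio 1.0), but the recorded dose in one arm is shifted by an assumed number of SDs.

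| Shift in recorded dose | Pooled AUC | AUC within each arm |
|---|---|---|
| 0 | 0.740 | 0.741, 0.739 |
| 1 SD | 0.715 | 0.742, 0.742 |
| 2 SD | 0.665 | 0.742, 0.743 |
| 3 SD | 0.633 | 0.741, 0.741 |

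A 1 SD scale shift with no modality effect moves the pooled AUC by 0.740 - 0.715 = 0.025. That is more than the 0.008 produced in step 3 by an odds ratio of 0.25.

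**5. Precision of within-group AUCs.** Hanley-McNeil: SE² = [A(1-A) + (n1-1)(Q1-A²) + (n0-1)(Q2-A²)] / (n1·n0), with Q1 = A/(2-A) and Q2 = 2A²/(1+A). Take A = 0.70 (assumed), so that A(1-A) = 0.21, Q1-A² = 0.0485 and Q2-A² = 0.0865.

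- 30 patients, assumed 30% event rate (9 and 21): (0.21 + 8×0.0485 + 20×0.0865)/189 = 0.0123, SE = 0.11. A 95% interval is 0.70 ± 1.96×0.111, about 0.48 to 0.92.
- 30 patients, 10% (3 and 27): 2.555/81 = 0.0315, SE = 0.18. At 50% (15 and 15): 2.099/225 = 0.0093, SE = 0.10.
- 6 patients, that is 30/5 if the five CIRT centres enrol equally (an assumption), 30% rounded to 2 and 4: (0.21 + 1×0.0485 + 3×0.0865)/8 = 0.0647, SE = 0.25.

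**The case against.** The case for leaving the text alone has several parts.

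- **It is only exploratory, and arm contrasts are planned elsewhere.** True. Functional QOL has its t test, 3-year local control in arms 1 and 3 has its own comparison, and clinical outcomes have Kaplan-Meier with likelihood ratio tests. Sequelae have logistic regression. This limits the consequence, but it does not make the AUC an estimate of a modality effect.
- **The sentence may loosely mean the effect of dose within each modality.** That would be a sound use of an AUC, but it is not what is written.
- **Different RBE models are already handled.** Largely right within CIRT. A reader might infer that the plan will pool DVHs across centres and derive dose cut-offs that really identify the centre. The documents do not support this: no pooled cut-off is planned, and CIRT data are to be analysed by institution. Nor do they show that doses will be on different scales at analysis. The centralised dose files would allow recalculation, and the full protocol may specify it. What stands is conditional: any CIRT-proton combination needs a common scale first.
- **AUC can be adapted to QOL and survival.** Also right. A reader might infer that an AUC is undefined for these outcomes, but QOL can be dichotomised, local control is also analysed as a 3-year proportion, and time-dependent ROC methods exist. Which form is used may be left to a fuller document.
- **The size of any distortion is not established.** Correct. The simulation kept a real dose effect, and in it a scale shift pulled the AUC towards 0.5. It does not show a spurious AUC arising with no dose effect.

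**Conclusion.** The point holds as an error in the stated purpose of one exploratory analysis. An AUC of a DVH measure does not determine a modality effect for any of the four outcomes named; that follows from its definition and needs no assumed figure. Two facts in the article reinforce it: patients treated by surgery alone have no DVH, and the by-institution rule leaves one modality in each CIRT analysis. The dose-scale part applies only if CIRT and proton patients are combined without harmonisation.

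The effect on the trial is small: no primary or secondary conclusion depends on this sentence. The simulated AUCs rest on an assumed dose slope, baseline risk and scale shift. The precision figures rest on an assumed AUC of 0.70, assumed event rates and, for single centres, an even split.

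**What to change.** Reword the sentence in section 2.6 along these lines:

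> *ROC-AUC will be reported for DVH measures solely as a description of discrimination among irradiated patients. It will be computed within modality and, for CIRT, within institution or RBE model. CIRT and proton patients will not be combined unless doses have been placed on a common scale. Exploratory effects of treatment modality will be estimated by regression with a treatment-arm term: logistic for sequelae, linear for change in QOL, and Cox for local control and survival.*

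The text should not simply defer to adjusted arm comparisons, because the article describes none; its primary comparison is a two-sample t test. The logistic model for sequelae is already planned and needs only an explicit arm term. Leaving DVH terms out of these arm models lets all three arms contribute, including patients who had surgery alone.

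The cost is a wording change and a few regressions on data already being collected. Recalculating doses on a common scale is needed only if the team wants to combine CIRT and proton patients; the documents give no basis for pricing that work. The downside is small groups: within-group AUCs will have wide intervals, and a single CIRT centre with about six patients would yield an essentially uninformative one. More elaborate modelling within groups of that size would not help.

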**Abstract:**

Surgical treatment of pelvic sarcoma involving the bone is the standard of care but is associated with several sequelae and reduced functional quality of life (QOL). Treatment with photon and proton radiotherapy is associated with relapse. Carbon ion radiotherapy (CIRT) may reduce both relapse rates and treatment sequelae. The PROSPER study is a tricontinental, nonrandomized, prospective, three-arm, pragmatic trial evaluating treatments of pelvic sarcoma involving the bone. Patients aged at least 15 years are eligible for inclusion. Participants must have an Eastern Cooperative Oncology Group Performance Status score of two or less, newly diagnosed disease, and histopathologic confirmation of pelvic chordoma, chondrosarcoma, osteosarcoma, Ewing sarcoma with bone involvement, rhabdomyosarcoma (RMS) with bone involvement, or non-RMS soft tissue sarcoma with bone involvement. Treatment arms include (1) CIRT (*n* = 30) delivered in Europe and Asia, (2) surgical treatment with or without adjuvant radiotherapy (*n* = 30), and (3) proton therapy (*n* = 30). Arms two and three will be conducted at Mayo Clinic campuses in Arizona, Florida, and Minnesota. The primary end point is to compare the 1-year change in functional QOL between CIRT and surgical treatment. Additional comparisons among the three arms will be made between treatment sequelae, local control, and other QOL measures.

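### The AUC of a DVH measure is named as the way to determine the effect of treatment modality, but it measures how well organ dose discriminates outcome and cannot estimate a modality effect

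*Protocol article*

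**What the plan says.** Section 2.6 of the protocol article has a paragraph of exploratory analyses. Its first sentence covers local control in arm 2 against arms 1 and 3, treatment sequelae, and DVH data, and says these "will be performed with standard logistic regression analysis of acute- (<6 months) and late-onset (≥6 months) treatment sequelae". A between-arm contrast is spelled out there for local control only. The next sentence adds a second method, ROC AUC analyses, and gives its purpose: they are done "for each DVH measure to determine the effect of the treatment modality on treatment sequelae, QOL, local control, and survival".

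Section 2.4 gives the source of the DVHs. It starts from "After treatment is completed, the full radiation data set", and DVHs "will be provided for the following OARs: the small bowel, large bowel, cauda equina, sacral plexus", followed by the femoral heads, rectum and bladder: seven organs at risk. No target-volume DVH is listed.

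Arm 2 is described in the Abstract as "surgical treatment with or without adjuvant radiotherapy", and section 2.2 states: "Adjuvant radiotherapy and/or chemotherapy will be allowed according to institutional approaches to treatment". Radiotherapy in arm 2 is therefore optional.

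On comparability of dose, section 2 says that the CIRT centers "use different RBE dose calculation models, dose fractionation schemes, and target volumes". Section 2.6 plans to analyse CIRT data by institution. It gives no rule on whether CIRT and PT are combined in the AUC analysis.

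**The concern.** The sentence names a method and a purpose that do not fit. The predictor in the AUC is a dose measure; treatment arm appears nowhere in it. A high AUC means that dose ranks patients well by outcome. It says nothing about whether CIRT, PT or surgery leads to more or fewer events. Surgery as a modality is also out of reach, because surgical patients without adjuvant radiotherapy contribute no DVH and those with it are a selected part of arm 2.

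The consequence is sharpest for treatment sequelae. Section 2 puts sequelae, CIRT against surgery, in the primary aim, and the Abstract promises a three-arm comparison of them. The primary t test, however, uses only the PROMIS-29 functional domain, and the logistic regression sentence states no arm contrast for sequelae. The AUC sentence is then the only method in section 2.6 expressly aimed at the effect of modality on sequelae. Followed literally, it would let a dose-discrimination result be reported as a modality effect.

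**Working it through.** **The plan's own figure.** The article gives no figure for the AUC analysis. Its only design figure is 30 per arm for the primary test (means -2 and -4.6, so a difference of 2.6; SD 4; one-sided α 0.05; power 80%). n = 2 × (1.645 + 0.842)² × 4² / 2.6² = 29.3, rounded up to 30; the noncentral t power at 30 per arm is 0.800. It reproduces, and nothing below changes it.

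**What the statistic contains.** AUC = P(D_case > D_non-case) + ½ P(D_case = D_non-case), where D is the DVH measure. Only D and the outcome enter.

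**Does the AUC follow the modality effect?** The inputs are assumptions, not figures from the article: binary outcome, normally distributed dose with SD 1, two equal radiotherapy arms, 400,000 simulated patients per arm.

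| Scenario | Risk, CIRT vs PT | AUC in each arm | Pooled AUC |
|---|---|---|---|
| A. Dose unrelated to outcome, same dose distribution | 20% vs 40% | 0.50, 0.50 | 0.50 |
| B. Dose predictive (log-odds slope 1 per SD), same dose distribution | 33% vs 33% | 0.74, 0.74 | 0.74 |

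A 20-point modality effect gives 0.50; no modality effect gives 0.74. Setting the arm-specific AUCs side by side does not help: their difference is zero in both rows, although the modality effect is 20 points in one and nil in the other.

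**If CIRT and PT were pooled.** Take risks of 20% and 40%, no dose effect within either arm, and doses 1 SD higher in the 40% arm.

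- Share of cases from the higher-dose arm: 0.40 / (0.20 + 0.40) = 2/3.
- Share of non-cases from that arm: 0.60 / (0.80 + 0.60) = 3/7.
- Case and non-case from the same arm: 2/3 × 3/7 + 1/3 × 4/7 = 10/21, with P(case dose higher) = 0.5.
- Case from the higher-dose arm, non-case from the other: 2/3 × 4/7 = 8/21, with probability Φ(1/√2) = 0.760.
- The reverse pairing: 1/3 × 3/7 = 3/21, with probability 0.240.
- Pooled AUC = 10/21 × 0.5 + 8/21 × 0.760 + 3/21 × 0.240 = 0.56, against 0.50 within each arm.

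With the dose shift reversed it is 0.44. Masking is possible too: with a dose slope of 0.7, doses 2 SD apart against the risk gradient, and risks of 22% vs 41%, simulation gave 0.68 within each arm and 0.53 pooled.

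**At the size of this trial.** Two arms of 30 give 60 patients. At the average risk of 30% there are 18 cases and 42 non-cases. The null standard error of the AUC is √[(n1 + n0 + 1) / (12 n1 n0)] = √[61 / (12 × 18 × 42)] = 0.082, a 95% half-width of 1.96 × 0.082 = 0.16. A pooled AUC of 0.56 would be hard to tell from 0.50.

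**The case against.** The strongest reply is that this is one loosely worded purpose clause in an exploratory paragraph, and that the comparisons that matter are made elsewhere. Most of that stands. Section 2.6 compares the PROMIS-29 functional score between arms by t tests, local control in arms 1 and 3 by a noninferiority test, and local control in arm 2 against the others by logistic regression. It evaluates time-to-event outcomes by arm with Kaplan–Meier and likelihood ratio tests. A reader might infer that the trial has no valid modality contrast; that is not so. It is also fair to say that the logistic regression may have been meant to carry arm for sequelae, but the sentence does not say so.

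A reader might also infer that CIRT and PT will be pooled and the AUC thereby confounded, or that any modality reading requires pooling. The article never states pooling, and its plan to analyse CIRT by institution points away from it. AUCs could be computed by arm, which avoids the confounding, though they still would not estimate a modality effect. The pooled figures are therefore hypothetical, come from assumed inputs, and are small against the sampling error at 60 patients.

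Nor can one say that all of arm 2 lacks DVHs. Thirty of 90 patients (36 of 108 with the planned over-recruitment) is a ceiling that supposes no adjuvant radiotherapy; the article gives no rate.

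A full protocol or analysis plan may hold more detail. That does not answer the point, because the purpose attached to the AUC is stated wrongly here, not left out.

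**Conclusion.** The point holds as a mismatch between method and stated purpose in an exploratory analysis. The AUC of a DVH measure cannot estimate the effect of modality on any of the four outcomes, and unirradiated surgical patients cannot enter it at all. This follows from the definition of the statistic and from the source of the DVHs, and needs no numerical assumption. The 0.50 and 0.74 illustrate it under assumed risks.

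Its weight is modest but real. It bears mainly on treatment sequelae, which belong to the primary aim as worded but have no other stated between-arm method. It leaves the primary test, the sample size, and the comparisons of functional QOL, local control and survival untouched. The risk that a pooled AUC creates or hides a dose association is conditional on a pooling step that the article does not describe.

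**What to change.** Reword the AUC sentence in section 2.6 and add one clause to the sentence before it.

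1. DVH AUCs: compute them within each radiotherapy modality, or stratified by modality so that only patients of the same arm are compared. Report them as dose-outcome discrimination and never as an effect of modality. Analyse arm 2 patients who received adjuvant radiotherapy apart.
2. Effect of modality on treatment sequelae: use the logistic regression already planned for acute and late sequelae, with treatment arm as the explanatory variable and surgery included.
3. Other outcomes: rely on the existing between-arm analyses.

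The change is wording and a few lines of code, with no new data. The price is precision. With 30 patients in an arm and an assumed 30% risk (9 cases, 21 non-cases), the null standard error of a single-arm AUC is √[31 / (12 × 9 × 21)] = 0.117, a half-width of 0.23. Averaging two such arms gives 0.117 / √2 = 0.083, close to the 0.082 of the pooled analysis. The stratified form therefore costs almost nothing; separate AUCs per arm are visibly wider.

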In the PROSPER study, patients with unresectable tumors will be enrolled in the trial, although they will not be eligible to be randomly assigned to the surgical treatment arm. Although randomization between the CIRT and PT treatment arms would potentially be possible, the logistics of randomizing these arms would still pose challenges. The PROSPER study protocol was activated at all 3 Mayo sites in 2022: at Mayo Clinic in Florida on 20 January, Mayo Clinic in Arizona on 14 February, and Mayo Clinic in Minnesota on 1 June. The participating CIRT sites are currently preparing to activate the trial. To date, no patients have been enrolled in the PROSPER study. We anticipate that the enrollment period will require up to 36 months for accrual. 

Mayo Clinic will enroll most of the patients in the trial but will not have the ability to treat patients with CIRT until 2027, when Mayo Clinic in Florida will open its CIRT center to patients. Although Mayo Clinic investigators could send patients to Europe or Asia to receive CIRT, treatment costs and travel restrictions would be challenging because the reimbursement of costs associated with sending patients abroad is currently unresolved for CIRT. Indeed, during the development of the PROSPER study, a randomized trial led by the University of Texas Southwestern Medical Center assessing CIRT vs. intensity-modulated radiotherapy/PT treatment of patients with pancreatic cancer (NCT03536182) was opened, closed, and withdrawn when the COVID-19 pandemic restricted travel, as well as the ability to randomly assign US patients to centers with CIRT in Europe and Asia.

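### DVH measures are related to local control and survival by ROC-AUC, a yes/no method with no stated horizon or censoring rule, although the same section treats these outcomes as time-to-event (minor)

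*Protocol article*

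**What the plan says.** All of this is in the protocol article, section 2.6 (Statistical Consideration), unless noted.

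- **Time-to-event treatment.** "The Kaplan–Meier method with likelihood ratio tests will be used to evaluate all clinical outcomes", and these outcomes include "local recurrence, regional progression, distant metastases, progression-free survival, and overall survival, for each treatment arm". The paragraph ends by calling these analyses time-to-event.
- **ROC-AUC.** The next paragraph plans analyses of the area under the ROC curve "for each DVH measure to determine the effect of the treatment modality on treatment sequelae, QOL, local control, and survival". It names no time point, no time-dependent version and no rule for patients whose follow-up ends early.
- **Logistic regression.** The sentence before that begins "Exploratory analyses of local control between arm 2 and arms 1 and 3, treatment sequelae, and DVH data will be performed with standard logistic regression" but closes by naming acute and late treatment sequelae as what is analysed.
- **The only fixed horizon.** Local control at 3 years is specified for the comparison of arms 1 and 3, once the last treated patient has 3 years of follow-up.
- **Follow-up.** Section 2: "We anticipate that the enrollment period will require up to 36 months for accrual"; the three Mayo sites opened between January and June 2022, while "The participating CIRT sites are currently preparing to activate the trial". Section 2.5 schedules visits from 3 to 60 months. Section 2.6 adds 6 patients per arm (30 to 36) for screening failure, loss, death and other causes up to 5 years.

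**The concern.** An ordinary ROC curve compares patients who had the event with patients who did not. Local control and survival have no such status until a time is chosen. If status is taken as recurred or died by last contact, a patient seen free of recurrence at 8 months counts the same as one seen free at 60 months, and a recurrence at 4 months counts the same as one at 50.

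Two things follow. Timing information is lost, in an analysis of about 60 radiotherapy patients with few events. And if follow-up length is related to the DVH measure, for instance because both differ between CIRT and proton therapy, length of observation can look like a dose association.

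At stake is the plan-level dose evidence. Section 2 says the centralised CIRT plans will be examined for patterns that go with local recurrence, and section 3 expects the results to help design later Phase III end points.

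**Working it through.** **The plan's own figures.** No power or precision is stated for the DVH analyses. The one stated power (80%, 30 per arm, difference 4.6 − 2 = 2.6, SD 4, one-sided α 0.05) reproduces: n = 2 × (1.645 + 0.842)² × 4² / 2.6² = 29.3, so 30 per arm. This point does not depend on it.

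**Loss implied by the plan.** 6/36 = 16.7% over 5 years for all causes; per year, 1 − (30/36)^(1/5) = 3.6%. By comparison, yearly losses of 10%, 15% and 20% accumulate to 1 − 0.90⁵ = 41%, 1 − 0.85⁵ = 56% and 1 − 0.80⁵ = 67%.

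**Why ever-event status depends on follow-up.** With constant hazard λ and follow-up C, P(event seen) = 1 − exp(−λC). Even with no dose effect this rises with C. Take an assumed 75% 3-year control: λ = −ln(0.75)/36 = 0.00799 per month.

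- CIRT entry in months 12–36, proton entry in months 0–36, analysis at month 72, follow-up capped at 60 months, no loss: mean follow-up 48 versus 52 months. P = 1 − exp(−0.384) = 0.32 versus 1 − exp(−0.416) = 0.34. The gap is small.
- Near-disjoint accrual plus loss of 15% versus 5% per year: mean follow-up about 33 versus 51 months. P = 1 − exp(−0.264) = 0.23 versus 1 − exp(−0.408) = 0.33. The gap is material.

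(These use mean follow-up in place of its distribution, as an illustration.)

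**Simulation.** From the document: 30 patients in each of arms 1 and 3, 36-month accrual, 60-month cap. Assumed: CIRT entry in months 12–36, analysis 36 months after last entry, 75% 3-year control, exponential event and loss times, one DVH measure with hazard ratio 1.6 per SD. The comparison is a Mann–Whitney test of the AUC on ever-event status against a Cox score test on the same data.

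Power with a true dose effect:

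| Loss per year, CIRT / proton | Dose gap and direction | AUC | Cox |
|---|---|---|---|
| 3.6% / 3.6% | none | 46% | 51% |
| 3.6% / 3.6% | CIRT 1 SD higher, higher dose protects | 58% | 61% |
| 3.6% / 3.6% | CIRT 1 SD higher, higher dose harms | 53% | 61% |
| 10% / 10% | none | 41% | 47% |
| 15% / 5% | CIRT 1 SD higher, higher dose harms | 38% | 56% |
| 20% / 5% | CIRT 1.5 SD higher, higher dose harms | 37% | 63% |
| 20% / 5% | CIRT 1.5 SD higher, higher dose protects | 76% | 63% |

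Rows with different dose gaps should not be compared with each other; the contrast is within a row. In the last row the AUC test rejects more often than Cox because the follow-up bias adds to the true effect.

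No true dose effect (nominal 5%):

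| Loss per year, CIRT / proton | Dose gap | Mean AUC | False positives |
|---|---|---|---|
| 5% / 5% | 1 SD | 0.496 | 5.6% |
| 10% / 5% | 1 SD | 0.485 | 5.1% |
| 15% / 5% | 1 SD | 0.476 | 5.8% |
| 20% / 5% | 1.5 SD | 0.457 | 7.6% |
| 20% / 5%, 60% 3-year survival | 1.5 SD | 0.45 | 9.1% |

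Cox stays near 5% in the two 20% / 5% settings. A harsher case (CIRT entry in months 24–36, proton in months 0–24, loss 15% versus 5%, dose 2 SD apart, 50% 5-year risk) gives AUC 0.44 and 11.7% false positives, against 5.3% for Cox.

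**The case against.** **A fuller protocol or SAP may fix the horizon.** An article need not give every detail, and the ROC wording does not exclude a 3-year or time-dependent version. Three-year status is already used for arms 1 and 3, and at the planned analysis every patient could have reached 3 years, so administrative censoring would go. This stands in part. In the 20% versus 5% setting a 3-year status brings false positives to 4.8% (early losses excluded) or 5.1% (counted as controlled), though mean AUC still shifts, to 0.53 or 0.47. Power is not fully restored. In the 10%/10%, 15%/5% and 20%/5% settings it is 35%, 38% and 39% with early losses counted as controlled, or 35%, 47% and 61% with them dropped, against 47%, 56% and 64% for Cox. And the point is not a missing detail alone: the text names a yes/no method for outcomes that the preceding paragraph treats as time-to-event.

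**Logistic regression.** A reader might infer that local control of surgery versus the radiotherapy arms is fixed to logistic regression. The documents do not establish this. The sentence opening "Exploratory analyses of local control between arm 2 and arms 1 and 3" ends with sequelae as the outcome of the logistic model, and Kaplan–Meier for local recurrence already covers every arm, including arm 2. It is an ambiguity to clear up, not an error shown.

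**The harmful scenarios are severe.** This stands. Loss of 10–20% per year is far above the roughly 3.6% the plan allows for all causes. Near that rate false positives stay at about 5%, and later opening of CIRT sites alone, with entry in months 12–36, does not produce a false association.

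**The analyses are exploratory.** This also stands and limits the weight.

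**Conclusion.** The point holds as a minor one. The stated ROC-AUC analysis of local control and survival does not fit how section 2.6 otherwise treats these outcomes.

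Its certain cost is a modest loss of power: 3 to 8 percentage points near the plan's own loss allowance, and 6 points at 10% loss per year, with equal loss in both arms. Its conditional cost is bias. If follow-up differs clearly between modalities and dose does too, associations can be masked, exaggerated or created, with false positives of about 8–9% under the assumed 20% versus 5% loss and a 1.5 SD dose gap.

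A reader might go further and infer that unequal follow-up will create or hide dose effects in this trial. The documents do not support that: they give no loss rates by arm and no DVH distributions, and under mild imbalance the error rate is nominal. Nor are the main results at risk through this route. The PROMIS-29 comparison, the 3-year local-control comparison and the arm-level Kaplan–Meier results do not use ROC-AUC.

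Event rate, hazard ratio, loss rates and dose separation are all assumptions, as is reading the AUC as based on ever-event status.

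**What to change.** 1. For local control and survival, replace ROC-AUC with Cox models that take the DVH measure as a continuous covariate, cause-specific for local recurrence.
2. If a discrimination index is wanted, use a censoring-weighted time-dependent AUC at 3 years, matching the horizon already set for arms 1 and 3.
3. Keep ROC-AUC for yes/no treatment sequelae.
4. Split the logistic sentence, so that logistic regression applies to acute and late sequelae and the exploratory comparison of local control between arm 2 and arms 1 and 3 uses the time-to-event framework already planned.

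The cost is a change of wording in the analysis plan and standard software. Event and last-contact dates are already needed for Kaplan–Meier, so no new data are required.
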